## Abstract

**Introduction::**

Septic shock is a potentially fatal organ dysfunction caused by an imbalance of the host response to infection. The changes in microcirculation during sepsis can be explained by the alterations in the endothelial barrier function. Endothelial progenitor cells (EPCs) are a potential recovery index of endothelial function and it an increase in response to neuromuscular electrical stimulation (NMES) was demonstrated. Therefore, the objective of this study is to investigate the effects of NMES in patients with septic shock.

**Methods and analysis::**

It is a study protocol for a randomized cross-over design in an intensive care unit of a tertiary University hospital. Thirty-one patients aged 18 to 65 years. The study will be divided in 2 phases: the phase one will be held in the first 72 hours of septic shock and the phase two after 3 days of first assessment. Patients will be randomly selected to the intervention protocol (decubitus position with the limbs raised and NMES) and control protocol (decubitus position with the limbs raised without NMES). After this procedure, the patients will be allocated in group 1 (intervention and control protocol) or group 2 (control and intervention protocol) with a wash-out period of 4 to 6 hours between them. The main outcome is mobilization of EPCs. The secondary outcome is metabolic and hemodynamic data. A linear mixed model will be used for analysis of dependent variables and estimated values of the mean of the differences of each effect.

## Introduction

1

Septic shock is a potentially fatal organ dysfunction caused by an imbalance of the host response to infection. The incidence of septic shock is 18.6 cases per 1000 hospital admissions with a mortality rate of 50.7% in the United States of America.^[1]^ According to international guidelines, patients with septic shock can be identified with clinical signs of sepsis and persistent hypotension requiring a vasopressor to maintain mean arterial pressure ≥ 65 mm Hg and serum lactate levels >2 mmol/L (18 mg/dL) despite adequate fluid resuscitation.^[2–4]^

Changes occur during sepsis in microcirculation, and consequently, there is a decreased blood supply resulting in organ dysfunction. This fact can be explained by the alterations in endothelial barrier function during disease.^[5]^ Indeed, the endothelium is responsible for the interface between tissues and the blood compartment and participates in the local regulation of blood flow and vascular caliber.^[6]^ Studies on the endothelial function and endothelial progenitor cells (EPCs) have been carried out in different groups of patients with metabolic syndrome, cardiovascular disease, in hemodialysis patients as well as in healthy individuals.^[7–9]^ The EPCs are a specific subtype of hematopoietic stem cells that can migrate from the bone marrow into the peripheral circulation. These cells are a potential recovery index of endothelial function and play an important role in neovascularization, repair, and restoration of the endothelium.^[8]^

In addition, it is common to use sedation and mechanical ventilation in septic shock patients. The frequent use of sedation limits mobilization of critically ill patients usually showing a progressive loss of muscle strength and functionality. Physiotherapy can use different techniques to help these patients increase muscle strength, recovery of functional status, decrease the length of weaning of mechanical ventilation, and decrease the duration of delirium.^[10,11]^ One of these techniques used to recruit muscles in the intensive care environment is neuromuscular electrical stimulation (NMES). The NMES is directed to those patients who cannot cooperate with physiotherapy due to sedation or decreased muscle strength, and it allows the patients to perform exercises in passive, assisted, and active modes.^[12]^ This noninvasive therapy is applied regardless of the patient's effort and produces a muscle contraction in response to a externally generated low-voltage electric impulse, which is conducted through electrodes placed on the skin over the muscle group to be stimulated.^[12,13]^

Some studies have shown evidence that the electrical stimulation reduces muscle atrophy and the time of weaning from mechanical ventilation and therefore increases muscle strength in critically ill people^[14–16]^; beneficial results of NMES have been demonstrated in patients with sepsis. In these patients, Rodriguez et al^[17]^ showed improved muscle strength—especially those in critical condition. Stefanou et al^[18]^ demonstrated an increase in EPCs after NMES. In patients with septic shock, only 1 study has evaluated the effects of NMES^[19]^; it demonstrated a marked decrease in the quadriceps volume independently of the use of NMES. However, the benefits of NMES are not limited only to the maintenance of muscle strength.^[14,15]^ Literature findings suggest that there is a potential benefit of NMES in acute activation of microcirculation observed by the increased rate of oxygen consumption and reperfusion as measured by infrared spectroscopy.^[20,21]^

Combining the pathophysiology of septic shock, the role of EPCs, the effects of NMES, and the divergence of results of the studies using NMES in patients in septic shock, we hypothesized that NMES initiated an early phase of septic shock and could contribute favorably to the mobilization of EPCs without causing metabolic and hemodynamic impairments. Therefore, the objective of this study is to investigate the effects of NMES in patients with septic shock.

## Patients and methods

2

### Study design

2.1

This study is a randomized controlled crossover clinical trial with group 1 (starts with intervention and ends with control protocol) and group 2 (control and intervention protocol).

### Study participants and eligibility criteria

2.2

The patients admitted to the intensive care unit are eligible if they present in the first 72 hours after the diagnosis of septic shock according to the international consensus definition of septic shock. They should have stable hemodynamic through fluid resuscitation, vasoactive drugs, and mechanical ventilation as described above.

Exclusion criteria will include patients aged 18 years or less or over 65 years, pregnant women, brain death, neuromuscular diseases, or the use of a pre-existing neuromuscular blocker in the last 24 hours.

Contraindications for the use of NMES will include fractures, burns, skin lesions, systemic vascular impairment diseases such as systemic lupus erythematosus, thromboembolic disease, deep vein thrombosis (which was not therapeutically anticoagulated for more than 36 hours), lower limb amputations, cardiac pacemaker, thrombocytopenia less than 20,000/mm^3^, body mass index greater than 35 kg/m^2^, important lower extremity edema, agitation, and/or signs of pain during the electrical stimulation.

Contraindications to begin or continue NMES procedure will include the following: mean arterial blood pressure less than 65 mm Hg, use of vasopressor >50% of the maximum dose (dopamine >12.5 μg/kg per minute; vasopressin >0.02 U/min and norepinephrine >1 μg/kg per minute), heart rate <50 or >140 bpm, arrhythmias with hemodynamic consequences, myocardial ischemia, temperature <34^ o^C or >39^o^C, intracranial pressure >20 cmH_2_O, decrease in 10% peripheral oxygen saturation (SpO_2_) baseline value or <88% for more than 1 minute.

### Recruitment organization

2.3

All patients with a diagnosis of septic shock will be recruited at intensive care unit admission. An explanatory statement will be given and writing informed consent will be obtained before the commencement of the study. The author [name] will have final approval of a patient's eligibility for the study. If the relatives of the patients accept the invitation to participate in the study, then they will sign the informed consent form.

### Randomization and allocation

2.4

This study will follow the recommendations of the Consolidate Standards of Reporting Trials (CONSORT)^[22]^ and the study protocol followed the Stardard Protocol Items for Randomised Trials (SPIRIT).^[23]^ After the consent, [name] will evaluate and determine the eligibility of patients. Thus, [name] will not be involved with the assessment and interventions that randomly allocates the participants in 1 of the 2 groups through a simple randomization (random numbers generated by the computer). The allocation sequence will be hidden by [name] through sequential numbered opaque sealed envelopes. After this step, [name] will open the envelope and will start the protocol. Blood sample analyses will be blinded to [name], [name], and [name].

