#### Data analysis and management

2.8.5

All data will be entered electronically. There will be a subject identification code list and each participant will receive a participant study identification number. Confidential documents will be retained in the institution's computer in the laboratory. A password system will be utilized to control access. Back up of data will be kept in locked cabinets in the laboratory as well.

The data set will be described via tables and figures containing values expressed as mean, standard deviation, median, minimum, and maximum values. The mean effects of the protocol and the group differences for all outcomes will be calculated using linear mixed models to incorporate terms for the protocols, sequence, and periods; a term referring to the carryover effect will also be added in order to control these effects.^[32]^

The effects will be related to differences of values in relation to the protocols, the sequences and the periods and it will be measured considering the value from the first moment of protocol and the value in the second time. The effects are listed below:The Protocols: Protocol 1: referring to intervention. Protocol 2: regarding the control.Sequences/Groups: Sequence/group 1: Related the sequence at the beginning of the study with the decubitus position with the limbs raised and NMES and ending with decubitus position with the limbs raised without NMES (Group 1). Sequence/group 2: Related to the sequence at the beginning of the study with the decubitus position with the limbs raised without NMES and ending with the decubitus position with the limbs raised and NMES (Group 2).Periods: period 1: related to the time of the first procedure. Period 2: related to the moment of the second procedure.

Estimated values and 95% confidence intervals are used to evidence the possible effects related to the studied factors. The *P* value is used to identify whether or not there was an effect of the protocol, the sequence, and the period. The level of significance will be set at 5%. Statistical analysis will be performed through the R version 3 (2013-05-16) (The R Foundation for Statistical Computing, Vienna, Austria) and SAS version 9.2 (SAS Inc., Cary, NC).

The sample size of 31 patients was based on the study of Stefanou et al^[18]^ for the variable CD34 + CD133 +, CD45− with effective detection of 7.3/10^6^ cells, standard deviation of 10.2, 5% alpha, and power of 80%.

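### Simple randomisation of 31 patients to two sequences is valid, but random permuted blocks would recover a little precision cheaply (minor improvement, not an error)

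*Protocol article*

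**What the plan says.** Section 2.4 of the protocol article describes a process that "randomly allocates the participants in 1 of the 2 groups", carried out "through a simple randomization (random numbers generated by the computer" and concealed in "sequential numbered opaque sealed envelopes". It mentions neither blocks nor strata and does not state an allocation ratio.

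The Abstract gives the study size as "Thirty-one patients aged 18 to 65 years". Section 2.8.5 repeats it: "The sample size of 31 patients was based on the study" of NMES in sepsis that the article cites, "with effective detection of 7.3/10^6^ cells, standard deviation of 10.2, 5% alpha, and power of 80" per cent. The same section plans "linear mixed models to incorporate terms for the protocols, sequence, and periods", plus a carryover term.

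Sections 2.1 and 2.5 make the trial a two-sequence crossover. Each patient receives both protocols, separated by a wash-out of 4 to 6 hours.

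**The concern.** In a two-sequence crossover that adjusts for period, the protocol effect is estimated by comparing within-patient differences between the two sequence groups. Its variance is proportional to 1/n1 + 1/n2, which is smallest when the groups are equal. Unrestricted randomisation leaves n1 and n2 to chance, and with only 31 patients chance can move them noticeably apart.

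What is at stake is efficiency, not validity. The sample size is set for 80% power with no dropout allowance stated, so on one reading of its inputs there is little slack to give away. A restricted list would avoid most of the loss without adding patients or procedures.

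**Working it through.** **Inputs.** From the documents: N = 31, difference 7.3 per 10^6 cells, SD 10.2, alpha 5%, power 80% (section 2.8.5); simple randomisation to two groups (section 2.4). Assumed: two-sided test, 1:1 target, one 2x2 crossover. The design figure is not available, and how the two study phases enter the analysis is not modelled here.

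**Step 1: reproduce the plan's figure.** 2 × [10.2 × (1.960 + 0.842) / 7.3]² = 30.65, rounded up to 31. This formula gives the number per arm of a parallel comparison. It equals a crossover total if the SD of within-patient differences is 10.2 × √2 = 14.42, that is, with zero within-patient correlation. If 10.2 is itself the SD of differences, the same power needs 15.3, so 16 patients (18 with the t distribution). The article does not say which SD is meant, so both are carried forward.

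**Step 2: chance of imbalance.** The size of one group is Binomial(31, 0.5). The probabilities below count both tails.

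**Step 3: precision.** Variance = (SDdiff² / 4) × (1/n1 + 1/n2). Relative to 16:15, where 1/16 + 1/15 = 0.1292, the 20:11 split gives 1/20 + 1/11 = 0.1409, a ratio of 1.09. The effective number of patients is 4·n1·n2/31; at 20:11 it is 880/31 = 28.4, which is like losing 2.6 of 31.

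**Step 4: power.** Normal approximation: Φ(7.3/SE − 1.96), with SE the square root of the variance in step 3. At 16:15 with SDdiff 14.42, SE = 7.21 × √0.1292 = 2.59 and power is 80.4%.

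| Split | Chance of this or worse | Variance vs 16:15 | Power, SDdiff 14.42 | Power, SDdiff 10.2 |
|---|---|---|---|---|
| 16:15 | 100% | 1.00 | 80.4% | 97.8% |
| 18:13 | 47.3% | 1.03 | 79.4% | 97.6% |
| 19:12 | 28.1% | 1.05 | 78.4% | 97.3% |
| 20:11 | 15.0% | 1.09 | 76.9% | 96.8% |
| 21:10 | 7.1% | 1.14 | 75.0% | 96.1% |
| 22:9 | 2.9% | 1.21 | 72.5% | 95.1% |

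**Step 5: average over all splits.** The mean variance ratio is 1.035, so 31 × (1 − 1/1.035) ≈ 1 patient is lost. Average power under simple randomisation is 79.1% against 80.4% at 16:15 (SDdiff 14.42), a loss of 1.3 points. With SDdiff 10.2 it is 97.4% against 97.8%, a loss of 0.4 points. Noncentral t with 29 degrees of freedom gives 76.3% against 77.7%, and 96.5% against 97.0%.

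**Step 6: after the change.** Randomly mixed blocks of 2 and 4 gave 16:15 in all 50,000 simulated lists of 31. If blocks of 6 are included, the worst split is 17:14, with variance ratio 1.008.

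**The case against.** The case for leaving section 2.4 alone is substantial.

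- **No bias.** Simple randomisation is a legitimate method, openly described. Sequence and period are in the model, so an unequal split does not distort the protocol effect. This stands in full.
- **The loss is usually small.** About 72% of the time (100 − 28.1) the split is 18:13 or better, costing at most 2.6% in variance. If 10.2 is the SD of differences, power stays at 95% or more even at 22:9. This stands too. A reader might infer that the groups are likely to be badly unequal, but that describes only the tail: 22:9 or worse has a chance of about 3%.
- **Simple randomisation buys unpredictability.** A reader might conclude that it gives up precision for nothing. That is not so: with small blocks in an unblinded single-centre trial, staff may sometimes guess the next allocation. Settling eligibility before the envelope is opened does not fully answer this, because a guess would act at that earlier stage. Names are removed from the text, so the separation of roles cannot be fully checked. What limits the harm is that block sizes can be varied and kept undisclosed, and that foreknowledge reveals only the order in which a patient receives two protocols that both will be given.
- **The carryover term raises a larger question.** If it pushes the protocol estimate onto period 1 alone, with a between-patient SD of 10.2, power is about 51% at 16:15 and 48% at 20:11. Nearly all of that shortfall comes from the model, and blocking recovers only about 3 points. Carryover therefore does not make imbalance a serious problem in its own right.

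**Conclusion.** This is a cheap and minor improvement. The protocol contains no error or contradiction on this point. Simple randomisation of 31 patients carries a 15% chance of a 20:11 split or worse (variance 9% higher at 20:11) and an average variance loss of 3.5%. The average power loss is 1.3 points or 0.4 points, depending on which SD the article means.

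These figures assume a two-sided test, a 1:1 target, one 2x2 crossover and complete data. A reader might also infer that blocking would remove imbalance altogether. It fixes the split only at randomisation. Section 2.2 lists conditions that bar starting or continuing NMES, and section 2.5 foresees patients who discontinue in phase two, so the analysed groups may still drift apart.

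**What to change.** In section 2.4, replace simple randomisation with a computer-generated permuted-block list with a 1:1 target and randomly varied block sizes. The person who is independent of assessment and intervention should prepare the list, keep it in the same numbered envelopes, and not disclose the block sizes to enrolling or treating staff. Mixing 2 and 4 holds the split at 16:15 for 31 patients; adding 6 makes guessing harder and allows at worst 17:14.

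The cost is a new allocation list and about one sentence of protocol text, with no extra patients, procedures or analysis terms. The price is slightly more predictability. The change is best made before the first allocation, since the gain is too small to justify disturbing a sequence already in use.

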### Procedures

2.5

The study will be divided into 2 phases, the phase one will be held in the first 72 hours of septic shock; the phase two will be 3 days after the first assessment. Patients will be submitted in a random order to the intervention protocol (decubitus position with the limbs raised and NMES) and control (decubitus position with the limbs raised without NMES). The patients may be allocated in Group 1 (intervention and control) or group 2 (control and intervention) with a wash-out period of 4 to 6 hours between them as visualized in Fig. 1.

**Figure 1 F1:**
[figure not shown]
Protocol design.

The study has a short follow-up, and the second measurements will be done after 3 days. Patients who discontinue or deviate from protocol are in the second phase of study; only results of the phase one of the study will be analyzed. These results will demonstrate the acute effects of NMES in the first 72 hours after diagnosis of septic shock.

### Primary outcomes

2.6

#### Endothelial progenitor cells (EPCs)

2.6.1

To evaluate the EPCs, blood samples will be taken from an existing central venous access. The first 3 mL is discarded, and the remainder will be collected in 5 mL tubes with acid citrate and dextrose 5 minutes before the baseline and at the end of each protocol. The samples will be processed within 3 hours after collection and will be kept at 4°C during the procedure. The analysis will be performed by flow cytometry (BD Biosciences, FACS Canto ^TM^ II, EUA) and centrifuged at 700g for 20 minutes with no brake. The upper phase (plasma) will be removed gently and aliquoted at 0.25 mL. The lower phase containing the blood cells will be resuspended using 10 mL of cold 1 × PBS containing 0.5% (w/v) of BSA and 1.5 mM EDTA and it will be centrifuged again at 700g for 20 minutes with braking. The upper stage will be removed and discarded, the cell sediment will be resuspended, and 2.5 mL will be transferred to a separate tube and kept on ice.

Concurrently, 500 μL of sample will also be transferred in an isotype control and in 3 sample tubes with the appropriate antibodies. It will then be added to 9 mL of ACK lysis buffer to lyse red blood cells and incubated at room temperature (18°C–25°C) for 3 minutes. It will be washed twice with 9 mL cold 1 × PBS and finally centrifuged to 250*g* to 4°C with no brake for 5 minutes. Cell sediment will be resuspended twice in 500 μL of 1× PBS, and the samples will be filtered through 40 μm cell strainer in BD 5 mL Falcon tubes. Tubes will be kept at 4° C (or ice) in the dark before the flow cytometry. Different subpopulations of endothelial progenitor cells will be quantified by cellular markers by flow cytometry: CD34+/CD133+/CD45−, CD34+/CD133+/CD45−/VEDFR_2_e CD34^+^/CD45−/VEGFR_2_+.^[24,25]^ Nurses will receive a training in how blood sample will be taken, even as laboratory staff will be trained to evaluate cell progenitor endothelial.

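### Three unranked EPC subpopulations are listed as primary and only one is powered; the marker and phase that carry the mobilisation claim are not named

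*Protocol article*

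**What the plan says.** The Abstract of the protocol article states: "The main outcome is mobilization of EPCs". It names no cell population. Section 2.6, whose heading is in the plural, contains only EPCs. Section 2.6.1 says "Different subpopulations of endothelial progenitor cells will be quantified by cellular markers by flow cytometry" and lists three: CD34+/CD133+/CD45-, the same set with VEGFR2 (the marker name is garbled in the text), and CD34+/CD45-/VEGFR2+. None is placed above the others. Blood is drawn "5 minutes before the baseline and at the end of each protocol".

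Section 2.5 sets up two phases: "The study will be divided into 2 phases, the phase one will be held in the first 72 hours of septic shock", and the second follows three days after the first assessment. The text after Figure 1 adds that, for patients who discontinue or deviate in the second phase, "only results of the phase one of the study will be analyzed".

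On analysis, section 2.8.5 says: "The mean effects of the protocol and the group differences for all outcomes will be calculated using linear mixed models". The terms are protocol, sequence, period and carryover. Period there means the first or second procedure, and no term for phase is listed. P values are to show whether there is an effect of protocol, sequence or period. On the threshold: "The level of significance will be set at 5" percent. On size: "The sample size of 31 patients was based on the study of" an earlier trial, for the variable CD34+/CD133+/CD45- only (difference 7.3 per 10^6 cells, SD 10.2, alpha 5%, power 80%).

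**The concern.** Three places that should agree on one endpoint do not. The Abstract gives a concept, section 2.6.1 gives three measurements of it, and the sample size gives one of those three without calling it primary. No text says how many subpopulations must change, or in which phase, before the trial is said to show mobilisation.

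Two things are at stake. If a significant result on any of the three is taken as support, the error rate of the main claim is not the stated 5%. And unless a document that is not shown fixes the choice, the marker and phase that carry the headline could be settled once the data are known. The 80% power applies to one marker only.

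**Working it through.** **Inputs.** Three subpopulations (section 2.6.1); two phases (section 2.5); a 5% level, difference 7.3, SD 10.2, power 80% and 31 patients (section 2.8.5). Two-sided tests are assumed, in line with the 95% confidence intervals planned there. The correlation between tests is not given, so a range is shown.

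**Step 1: the plan's own figure.** The two-group formula gives

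n = 2 × [10.2 × (1.960 + 0.842) / 7.3]² = 30.65, rounded up to 31, with power 80.4% at 31.

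So 31 is reproduced for one variable at a two-sided 5% level, with nothing set aside for further tests. Strictly this is the per-arm number for two independent groups. It equals 31 crossover patients if 10.2 is the SD of a single measurement and the within-patient correlation is zero.

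**Step 2: independent tests, any one counting.**

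- Three tests: 1 − 0.95³ = 14.3%.
- Three tests, false increases only (2.5% each): 1 − 0.975³ = 7.3%.
- Six tests (three subpopulations × two phases): 1 − 0.95⁶ = 26.5%.

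**Step 3: correlated tests.** Jointly normal test statistics with equal correlation among subpopulations, 500,000 simulated draws, critical value 1.96. For six tests, the lower value has the two phases sharing the same correlation and the upper has them independent.

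| Assumed correlation | Three tests, either direction | Three tests, increase only | Six tests, either direction |
|---|---|---|---|
| 0 | 14.3% | 7.3% | 26.5% |
| 0.5 | 12.5% | 6.2% | 20.7–23.5% |
| 0.8 | 9.8% | 4.9% | 13.8–18.7% |
| 0.9 | 8.4% | 4.2% | 10.8–16.1% |

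The comparison value is 5% for the two-sided columns and 2.5% for the increase-only column.

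**Step 4: keeping everything co-primary.** With a Bonferroni split on the formula of step 1:

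- Three tests at 0.05/3 = 0.0167 each: n = 41 for 80% power; 31 gives 66%.
- Six tests at 0.05/6 = 0.0083 each: n = 48; 31 gives 57%.

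**The case against.** The strongest reply has four parts.

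- **Number of tests.** A reader might infer six primary tests, one per subpopulation and phase, with success on any one. The article does not say this. It describes two phases of conduct, not a confirmatory test in each, and it states no rule that one marker suffices. If all three markers had to be significant, the error rate would be at most 5%. Separate analysis by phase is plausible, because the listed model terms do not include phase, but it is an inference. This part stands: 26.5% is an upper figure on one possible reading.
- **Size.** A reader might also conclude that the chance of a false mobilisation claim is far above 5%. That needs independent tests or six of them. If the garbled marker is VEGFR2+, the four-marker population is contained in both others, so positive correlation is likely. Mobilisation also means an increase, and for false increases only the three-test figures are about 4% to 7%. This part stands too, although the benchmark for that count is 2.5%.
- **An unseen plan.** A statistical analysis plan or the full protocol may rank the markers or adjust for multiplicity. That is possible, and the absence of an adjustment method is not the complaint. The article does, however, give a primary-outcome section, a significance level and a powered variable, and these do not point to one endpoint.
- **The powered variable as implied primary.** CD34+/CD133+/CD45- is listed first and carries the sample size, so reading it as primary is reasonable. But the text never says so, and the plural heading and unranked list point the other way.

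**Conclusion.** The point holds as an undefined primary endpoint with moderate error inflation. Three unranked subpopulations are primary, one 5% level covers all outcomes, and only one subpopulation is powered. If each of the three is tested at 5% and any one counts, the two-sided family-wise error is about 8% to 14%, for assumed correlations from 0.9 down to 0. For false increases only it is about 4% to 7% against 2.5%. If both phases were also tested separately, the two-sided figure would be at most 26.5%, but the article does not state that analysis and the figure should not be quoted as what the plan does. The defect should be corrected whatever the exact correlation, since every scenario computed exceeds its nominal level.

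**What to change.** State in section 2.6 that the single primary endpoint is the NMES-versus-control comparison of CD34+/CD133+/CD45- in phase one, tested at 5%. This is the variable behind the sample size, and phase one is the part the article already lets stand alone when a patient discontinues or deviates later. Make the other two subpopulations in phase one and all three in phase two (five results) secondary. Report them as estimates with 95% confidence intervals and no claim of effect on their own, or adjust them by Holm's method. Bring the Abstract into line, and the registry entry too if it reads differently (it was not seen).

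The cost is a sentence or two. The sample size of 31, the 5% level and the power for the powered variable are unchanged, whereas the co-primary route would need 41 or 48 on the same formula. The downside is that an effect seen only on another marker, or only in phase two, would not count as primary success.
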